### Objectives 1-3:

The original survey was developed after collecting all other national CR program surveys and conglomerating items, and then soliciting input from the ICCPR community. The survey was revised from the previously-administered version to address objectives herein, and then soliciting input from the ICCPR community.

The survey assesses: (1) referral and access to the program; (2) program staff, facilities and components offered; (3) characteristics of any supervised model they deliver (e.g., type and

number of patients served, dose), (4) nature of any unsupervised delivery models, and (5) some final questions about quality improvement.

### Qualitative (Objective 3):

To characterize the sample of interviewees, prior to the interview, they will be asked to share their: country, occupation (i.e., stakeholder group), sex, and years working in cardiac area.

The semi-structured interview guide has been developed by the PIs; it focuses on barriers and enablers to accessible CR capacity increases. Prior to qualitative data collection, it was piloted in each region/income class, to enable contextual tailoring.

## **Data Analyses**

### Quantitative:

#### Objective 1 (GBD):

Current CR availability and capacity will be characterized descriptively at all analytic levels.

Changes in CR availability (i.e., none versus now have any) from the initial Audit at the country level will be quantified. The rapid COVID Audit did not focus on capacity indicators other than program closure due to the pandemic, and hence change from that Audit were not considered. Change from 2016 to present in percent of countries in each income class and region with any CR availability will be described.

CR capacity was a sum of supervised and unsupervised program capacity; only supervised capacity was considered in the initial Audit. Therefore, capacity changes will only be examined descriptively; for changes, the IHD only data will be used, and inferential tests will not be performed given the improved approach in capturing the indicated sample.

CR service levels and coverage will be computed as outlined above at all analytic levels. Coverage values will be ranked by country.

CR service shortfall/surplus and coverage values incorporate GBD incidence estimates. Their CR-indicated condition category changed from the initial Audit (ACS only to now IHD including also angina and ischemic-caused HF). Given also changes in the capacity measure (inclusion in current Audit of unsupervised capacity, these indicators will be juxtaposed by country descriptively from the first Audit estimates and change computed. Change from the first Audit by income class and region will be described, without inferential tests as above.

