Reasons for CR under-utilization are well-established, with factors from the patient to health system level at play. The major issue is lack of available programs to serve patients. Indeed, the International Council of Cardiovascular Prevention and Rehabilitation (ICCPR; PIs on Executive) – an umbrella organization of CR Societies globally- conducted a first Global Audit of CR programs in 2016/2017 which was the first ever to quantify program availability. Of 203 countries recognized by the World Health Organization (WHO), it was established for the first time that only 111 (55%) had any CR; only 17% of countries in Africa have any CR. Annual patient capacity in each program was ascertained and juxtaposed against ischemic heart disease estimate in every country of the world from the Global Burden of Disease (GBD) study revealing only one CR “spot” for every 12 new patients in need each year. Indeed, when summarizing across the globe, countries had a median of only 4 programs, and had capacity to serve a median of only 120 patients per year. Globally, 16.3 million more CR “spots” are needed each year to treat incident ischemic heart disease (IHD) patients, with 14 million of those spots needed in LMIC. For instance, India and China each need over 3 million more spots per year, with Russia 1.2.

ICCPR utilized the results from this first Audit to advocate for increases in CR capacity, with unmet CR need data for each country disseminated widely through national champions. In addition, resources to support development of quality programs, particularly in resource-poor settings, were created.

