### CR Program Sample (Obj 1-3):

The population consists of all phase 2 (as defined in North America) CR programs identified in the world. The sample will consist of all identified, consenting programs in the world. The most responsible clinician of the identified CR programs will be asked to complete the survey.

*CR Program Inclusion Criteria:* Post-acute care CR programs offering at least: (i) initial assessment, (ii) structured aerobic exercise (can be supervised or unsupervised; e.g., remote via technology) and (iii) at least one other component to control CV risk factors (e.g., patient education, psychosocial or dietary counselling, tobacco cessation). Setting can be residential, but is generally outpatient.

*Exclusion Criteria:* Programs that offer CR solely and temporarily as part of a research study. Phase I and maintenance programs.

*Qualitative (Obj 3):*

*Inclusion:* (a) Lead clinicians of existing CR programs, (b) Board members of CR-related societies, and (c) cardiac policy-makers, in countries with the greatest CR service shortfall (e.g., exceeding 250,000 patients per year), lowest CR coverage and/or largest reductions in capacity since the previous Audit will be eligible to participate.

*Exclusion:* Self-reported lack of proficiency in English, and for countries with CR, staff for whom CR is not in their job purview.

While sample size cannot be determined a priori, we are estimating 30 interviews to reach saturation of themes. When no new information is emerging upon concurrent interview coding, data saturation will be considered achieved.

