## **Measures**

*Quantitative:*

*Objective 1:*

Countries will be characterized by World Bank income class (i.e., 4) and WHO region (i.e., 6). Surveys without country specified were grouped together separately but maintained in the sample to promote generalizability. The indicators below will be aggregated at the country, region, income class and global analytic levels.

CR need: raw IHD incidence per country from latest Global Burden of Disease estimates (2023; <https://vizhub.healthdata.org/gbd-results?params=gbd-api-2021-permalink/6afc006e91ec18286cf82cec24bc38c1>), minus correction value as described below.

To conservatively take into account that some patients do not survive an incident event (e.g., 30-day survival) to the point of initiating CR or they suffer comorbidities which render them ineligible for CR (inability to ambulate, comorbid terminal condition, comorbid sensory or cognitive impairment), a correction was applied to national incidence values to represent a more true CR-eligible population estimate. Based on the literature showing inequality in CVD morbidity and mortality, we assumed that 85% of incident IHD patients in HICs would be eligible for CR, 80% in MICs, and 75% in LICs.

CR availability: existence of  $\geq 1$  program in a country (yes/no), with the total number of available programs ascertained by the national champions.

CR capacity refers to the number of patients a program reports they could serve annually. For each program, total capacity was computed as the sum of annual supervised and unsupervised capacity. For programs that offered either CR model but had missing or outlier (i.e.,  $>10,000$ ) capacity values, the median capacity for the WHO region of the country in which program is located was imputed. However, while not applicable for supervised models given number of responses, if  $<5$  programs within a region reported capacity for unsupervised CR, the overall median unsupervised program capacity across all MICs was applied (i.e., 75), as none of the remaining countries with missing data were classified as HICs and only 2 responding countries were LICs. Zero capacity reflects no availability.

Median program capacity was determined based on the total capacity values across all programs within that country. This was then multiplied by the number of programs in the country to ascertain national CR capacity.

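### Change since the first Audit compares supervised-plus-unsupervised capacity and a redefined need with supervised-only capacity and the older need, and no like-for-like change is planned

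*Protocol*

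**What the plan says.** All references are to the Protocol.

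- **Capacity (Data Analyses, Objective 1 (GBD)).** "CR capacity was a sum of supervised and unsupervised program capacity; only supervised capacity was considered in the initial Audit". Measures, Objective 1, confirms the current definition: "For each program, total capacity was computed as the sum of annual supervised and unsupervised capacity". National capacity is the country's median program total multiplied by its number of programs.
- **Need (same analysis section).** The condition category moved from "ACS only to now IHD including also angina and ischemic-caused HF". The Background (Evidence-practice gaps) describes the first Audit differently: capacity was "juxtaposed against ischemic heart disease estimate in every country of the world".
- **Eligibility correction (Measures, CR need).** For current need, "a correction was applied to national incidence values to represent a more true CR-eligible population estimate". The factors are 85% (high-income), 80% (middle-income) and 75% (low-income). The documents do not say whether the first Audit applied any such factor.
- **Change.** Capacity change is to be examined descriptively. Shortfall or surplus and coverage are to be set beside the first-Audit estimates by country, with change computed, and change is also described by region and income class. No tests are planned. A clause in the capacity paragraph says that only the IHD data will be used for changes.
- **Use of the change (Sample, Qualitative (Obj 3)).** One route to interview eligibility is being in a country with the "largest reductions in capacity since the previous Audit".
- **Unsupervised capacity (Data Analyses, Objectives 1-3 (Survey), Mode of CR delivery).** Unsupervised availability, capacity and reimbursement are to be compared descriptively with the previous Audits by country.

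**The concern.** The plan names two of the incomparabilities itself and then computes the difference anyway. Leaving out significance tests avoids a misleading p-value. It does not alter the difference, which mixes what happened on the ground with what was redefined. The eligibility correction is a possible third shift, and the analysis section does not list it among the changes.

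Objective (b) asks about the move from supervised to unsupervised or hybrid delivery. A change in total capacity against a supervised-only baseline merges that move with real gain or loss of places, so a country that lost supervised places can appear to have grown. The same capacity change feeds one of the criteria for choosing interview countries, and country summaries go to the Societies for advocacy.

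**Working it through.** The Protocol gives no change figure, power or sample size for this analysis, so there is nothing to reproduce. The steps below show how far definitions alone can move the result. Values of u and g are assumptions; the documents give neither.

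**1. Capacity.** Let S0 be first-Audit supervised capacity and S1 current supervised capacity, both as national figures. Let u be the part of the current total that unsupervised capacity adds, so the current total is S1/(1-u). Because the national figure is a median times a count, u must be read as 1 minus (supervised-only national figure / total national figure). It is not a simple sum over programs.

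Apparent change = S1/[S0(1-u)] - 1. With S1 = S0 this is u/(1-u):

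| u (assumed) | Apparent change | Supervised-to-supervised change |
|---|---|---|
| 0.10 | 0.10/0.90 = +11% | 0% |
| 0.20 | 0.20/0.80 = +25% | 0% |
| 0.30 | 0.30/0.70 = +43% | 0% |
| 0.50 | 0.50/0.50 = +100% | 0% |

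With a true supervised loss of 20%, S1 = 0.80 S0 and the apparent change is 0.80/(1-u) - 1. This is positive once u exceeds 0.20. At u = 0.30 it is 0.80/0.70 - 1 = +14%. In the same way, losses of 10% and 30% are masked once u exceeds 0.10 and 0.30.

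**2. A baseline for coverage.** The Background gives one place per 12 new patients and a global shortfall of 16.3 million places. From N/C = 12 and N - C = 16.3 million, C = 16.3/11 = 1.48 million, N = 12 x 1.48 = 17.8 million, and coverage is 1/12 = 8.3%. This serves only as a scale.

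**3. Eligibility factor alone**, if the first Audit applied none (assumption) and nothing else changed. Coverage becomes 8.33%/f and shortfall becomes f x 17.78 - 1.48:

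- f = 0.85: coverage 9.8%, shortfall 13.6 million
- f = 0.80: coverage 10.4%, shortfall 12.7 million
- f = 0.75: coverage 11.1%, shortfall 11.9 million

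**4. Wider need alone.** If current IHD need is g times first-Audit need, coverage becomes 8.33%/g: 5.6% at g = 1.5 and 4.2% at g = 2. If the first Audit already used IHD, as the Background says, g = 1 and this shift vanishes. The contradiction between the two sections therefore decides whether this component exists.

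**5. All three together.** With supervised capacity and disease frequency unchanged, coverage becomes 8.33% / [(1-u) x f x g]. At u = 0.20 and f = 0.80:

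- g = 1: 13.0%
- g = 1.5: 8.7%
- g = 2: 6.5%

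The sign turns at g = 1/(0.80 x 0.80) = 1.56. The same unchanged situation can thus be reported as a rise or a fall in coverage.

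**6. What is available.** The current survey yields supervised and unsupervised capacity per program, so a supervised-only national figure can be built. It has to be recomputed from supervised values, because a median of totals cannot be split afterwards.

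**The case against.** The strongest defence is disclosure. The plan names the capacity and condition changes, limits itself to description, and restricts changes to the IHD data, which may be meant to harmonise need. Part of this stands: the plan hides neither of those two changes. But the IHD clause sits in the paragraph on capacity, where no need term enters. It cannot repair the capacity mismatch, and it does not repair need if the first Audit used ACS only.

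A second defence is that total capacity is a legitimate measure of access, since a country that replaced supervised with unsupervised places may have lost nothing overall. That also stands, and it is a reason to keep total capacity as a secondary description. It does not justify comparing that total with a supervised-only baseline.

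Third, the survey section's comparison of unsupervised capacity with previous Audits comes close to a separate line for it. However, the Objective 1 analysis says that "only supervised capacity was considered in the initial Audit" and that the COVID Audit did not focus on capacity beyond closures, so the source of the comparator is unclear.

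Some stronger readings are tempting but not supported:

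- *Change is the main result of objective (a).* That objective is to update current status; change is not named in it.
- *The reported change will overstate progress.* Definition alone pushes capacity upward, but for coverage and shortfall the direction is unknown (step 5).
- *The eligibility factors inflate the change.* They do so only if the first Audit applied none, which the documents leave open.
- *Countries with real losses will be missed for interview.* Two other routes, largest shortfall and lowest coverage, rest on current status. A country is missed only if it fails both and its loss is masked.
- *Everything needed is already in hand.* This is firm only for current supervised capacity. Need on one definition at both dates requires a further GBD extraction.
- *Current need comes from the wrong year.* The address contains "gbd-api-2021-permalink" beside a 2023 label, but a fragment of an address does not establish which release was queried.

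**Conclusion.** The concern holds for the comparison over time. The plan computes change in capacity, shortfall and coverage across definitions that it says differ, and it offers no comparable version. With supervised capacity unchanged, definition alone shows capacity growth of u/(1-u), or +25% at u = 0.20, and hides a 20% supervised loss once u exceeds 0.20. For coverage the size and direction cannot be determined from the documents, because they depend on u, on g and on whether the first Audit corrected for eligibility.

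This should be fixed, but it is not critical. It concerns a disclosed, untested, secondary description and one of three routes to interview eligibility. Current availability, capacity, shortfall and coverage are unaffected.

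**What to change.** 1. **Capacity change.** Make the main comparison supervised to supervised: recompute each country's median from supervised values and multiply by its number of programs. State how programs with no supervised model enter the median and the count. Show unsupervised capacity as a separate line. Total-capacity change may stay as a secondary description, labelled as spanning two definitions.
2. **Change in coverage and shortfall.** Use one need for both Audits. Either set both supervised capacities against the same current corrected need, which shows only the part due to capacity, or use one GBD release, one definition and the same eligibility factors at both dates, if that extraction is available.
3. **Interview countries.** State which capacity change defines the largest reductions, and report the supervised-only change beside it.
4. **Wording.** Explain what restricting changes to the IHD data means. Reconcile the Background (first-Audit need as IHD) with the Objective 1 analysis (ACS only). Reconcile the survey section's comparison of unsupervised capacity with previous Audits against the statement that the first counted supervised capacity only. State whether the first Audit applied an eligibility correction.

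The cost is an extra set of spreadsheet columns from data already collected and, for the second option under item 2, one further GBD extraction. The work should be done before change results are produced.

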#### Objectives 1-3 (Survey):

Country and program response rates will be computed. SPSS version 31 will be utilized, analyzing all initiated surveys.

The number of responses for each question may vary due to missing data, such as instances where respondents did not answer a question due to legitimate inapplicability or the use of skip logic. For descriptive analyses, percentages will be computed using the number of valid responses for the specific item as the denominator.

Data cleaning was documented in an Audit trail. Given the small CR samples in some countries, except for the CR capacity variable, missing data will not be imputed. For continuous variables, outliers and implausible values were also reviewed and addressed as appropriate.

Descriptive statistics, including frequency with percentage (e.g., mode items) or median with quartiles (e.g., capacity) as appropriate, will be applied to analyze all closed-ended items in the survey. Open-ended items with responses from more than 10% of responding programs will be coded using content analysis.

*Mode of CR delivery:* A descriptive examination of responding program characteristics will be performed. Delivery mode availability will be described by country, and characteristics of hybrid delivery (e.g., technology, dose, comprehensiveness, multidisciplinary) by region and income class. Availability (yes/no) of unsupervised delivery specifically, and where yes capacity (patients served per year) and reimbursement (yes/no) will be compared descriptively to the previous Audits at a country level, with current income class, regional and global summary statistics computed. Regional and income class differences (independent variables) in the above parameters of capacity and reimbursement will be tested in an exploratory manner via generalized linear mixed models (GLMM), to account for clustering of programs, where country is the random effect. The models will be fitted via the Poisson distribution log link function.

*Objective 3 – Access and equity:* Strategies for referral of patients to the CR programs will be described by country, region, and income class, with a focus on eReferral. Barriers to broader delivery will be described in the same manner. Regional and income class differences (independent variables) in referral strategies and barriers (dependent variables) will also be tested each using GLMM as above.

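### One Poisson log-link model is fixed for every GLMM, although reimbursement is a yes/no item and capacity a skewed count; the cost in power runs from nil to large

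*Protocol*

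**What the plan says.** In the Protocol, Data Analyses, Objectives 1-3 (Survey), the paragraph on mode of delivery tests regional and income-class differences "in the above parameters of capacity and reimbursement will be tested in an exploratory manner via generalized linear mixed models (GLMM"), with the random effect there "to account for clustering of programs, where country is the random effect". It then fixes the family for all of them: "The models will be fitted via the Poisson distribution log link function". Just before this, the paragraph gives the scale of one outcome: "reimbursement (yes/no) will be compared descriptively to the previous Audits at a country level". Capacity is defined there as patients served per year.

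The Objective 3 paragraph carries the specification over: differences "in referral strategies and barriers (dependent variables) will also be tested each using GLMM as above". The response scale of these items is not given there or under Measures, which lists survey topics only.

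The predictors, World Bank income class (4 levels) and WHO region (6 levels), are both country-level (Measures, Objective 1). No binomial or negative binomial alternative, scale parameter or robust covariance is mentioned.

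**The concern.** The Poisson family ties the variance to the mean. For a 0/1 item that variance is too large: p in place of p(1-p). For program capacity it is far too small. In a model with a random country intercept the two errors act differently. With a binary outcome the assumed noise already exceeds the real noise, so nothing is left for the country term to explain and the tests can become conservative. With capacity, the unexplained spread between programs is pushed into the country term. The log link with a normal country effect also permits fitted probabilities above 1.

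At stake are the protocol's only inferential tests, since the Objective 1 section rules out inferential tests for changes since the first Audit. They support the comparison of access between income classes and regions, and an unsuitable family mostly makes such differences harder to see.

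**Working it through.** The protocol gives no alpha, power or sample size for these models, so there is no figure to reproduce.

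**Inputs from the protocol.** Poisson with log link; reimbursement yes/no; median unsupervised capacity 75 across MICs; capacity treated as an outlier only above 10,000; capacity summarised by median and quartiles; country as random effect; a median of 4 programs per country in the first Audit.

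**Assumptions (not in the protocol).** Two-sided 5% level, 90 countries, and the prevalences, country SDs and effects shown below.

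**1. Yes/no item, no clustering.** For a log prevalence from n programs the true variance is (1-p)/(np); Poisson uses 1/(np). The ratio of standard errors is 1/sqrt(1-p):

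- p = 0.1: 1/sqrt(0.9) = 1.05
- p = 0.3: 1/sqrt(0.7) = 1.20
- p = 0.5: 1/sqrt(0.5) = 1.41
- p = 0.7: 1/sqrt(0.3) = 1.83

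**2. Yes/no item, clustered by country.** Simulation A: two country groups, median about 4 programs per country, log odds ratio 0.6, random-intercept models by adaptive quadrature, model-based Wald test, 200 data sets per row. Monte Carlo error is about 1.5 points at 5% and 3.5 points at 50%.

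| Base rate | Country SD (logit) | Type I error, Poisson | Power, Poisson | Power, binomial |
|---|---|---|---|---|
| 0.3 | 0 | 2.5% | 87.5% | 96% |
| 0.3 | 0.5 | 5.5% | 74% | 77% |
| 0.3 | 1.0 | 8.5% | 49% | 46.5% |
| 0.5 | 0 | 1.5% | 75% | 92.5% |
| 0.5 | 0.5 | 5.5% | 64% | 78% |
| 0.5 | 1.0 | 8.5% | 49% | 55.5% |
| 0.7 | 0 | 0.5% | 19% | 84% |
| 0.7 | 0.5 | 0% | 27% | 74% |
| 0.7 | 1.0 | 4.5% | 33% | 45% |

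The ratio of mean model standard error to true SD was 1.17-1.98 at country SD 0, 0.94-1.57 at 0.5 and 0.86-1.08 at 1.0. The Poisson country SD collapsed to about zero in 42-100% of fits when the true SD was 0.5, and in 1-77% when it was 1.0. At country SD 1.0 the binomial Wald test was itself somewhat liberal (type I error 6.5-10%).

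Simulation B: more unequal country sizes (median 6 programs, range 1-250), four income classes with logit effects 0/-0.4/-0.6/-0.6, country SD 0.5, likelihood-ratio test, 500 replicates. Power, Poisson against binomial, was 58% v 60% at prevalence 0.50, 42% v 59% at 0.70 and 8% v 52% at 0.85. Poisson type I error was 1.8% at 0.70 and 0.4% at 0.85; the country variance was zero in 87% and 99% of fits.

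**3. Capacity: is Poisson plausible?** With mean 75 the Poisson SD is sqrt(75) = 8.7, so most programs in a country would report between 75 - 2 x 8.7 = 58 and 75 + 2 x 8.7 = 92. That does not fit a measure kept up to 10,000 and summarised by quartiles. Under a negative binomial the variance-to-mean ratio is 1 + mean/k: 38.5 at k = 2, 76 at k = 1 and 151 at k = 0.5.

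**4. Capacity: effect on the tests.** Simulation A (k = 1, log rate ratio 0.5):

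| True country SD (log) | Country sizes | Poisson country SD | Power, Poisson | Power, negative binomial |
|---|---|---|---|---|
| 0.3 | moderate | 0.65 | 95.5% | 99.5% |
| 0.3 | very unequal | 0.71 | 85.5% | 100% |
| 0.7 | moderate | 0.91 | 77% | 77% |
| 0.7 | very unequal | 0.95 | 67.5% | 79% |

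The Poisson standard error was 0.93-1.04 times the true SD and type I error was 4.5-6.0%, because the inflated country term absorbs the excess. Simulation B, at one setting (program log-SD 1.2, country SD 0.3, 120 replicates), gave a country SD of 0.75 and power of 78% against about 100%.

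**5. Why power falls: weights.** In that last setting, take capacity 75 and compare a one-program with a 200-program country.

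- Poisson: [1/(0.75² + 1/75)] / [1/(0.75² + 1/15,000)] = 0.5626/0.5758 = 98%.
- True variances: [1/(0.3² + 1.2²)] / [1/(0.3² + 1.2²/200)] = 0.0972/1.53 = 6%.

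Poisson thus gives the one-program country almost the same say as the large one.

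**The case against.** A reader might infer that every modelled outcome is yes/no, that all standard errors are wrong, and that real differences will routinely be missed. The protocol does not support this.

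- Only reimbursement is stated as yes/no. Referral strategies and barriers are probably tick-box items, but barriers could be ratings and strategies could be counts.
- For capacity, standard errors and type I error were close to nominal. What remains is inefficiency and a wrong country variance, which the plan does not say it will interpret.
- The large losses need prevalence of about 0.7 or more. The only hint on reimbursement, in the Background, is that remote programs were scantily reimbursed in 2020. If that still holds, p is low and the two families nearly agree.
- With country SD 1.0 the Poisson tests were not conservative at base rates 0.3 and 0.5.
- The mode-of-delivery tests are labelled exploratory. Strategies and barriers are also described by country, region and income class, and Objective 3 has about 30 planned interviews as well.

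All of this stands, and it limits severity. One further argument does not: that Poisson is acceptable for binary data with robust variance, so that only a detail for an analysis plan is missing. The protocol does not leave the family open. It fixes Poisson for all the models without the robust variance that would justify it for a declared yes/no outcome.

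**Conclusion.** The point holds at moderate severity. A single Poisson log-link specification does not match a declared binary outcome and is implausible for capacity.

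For yes/no items the loss of power depends on two quantities the protocol does not give. In Simulation A it was 0 to 8.5 points at base rate 0.3, 6.5 to 17.5 at 0.5, and 12 to 65 at 0.7, shrinking as country variance grows. Simulation B, with more unequal country sizes, gave 2 points at 0.50, 17 at 0.70 and 44 at 0.85. For capacity the loss was 0 to about 15 points in Simulation A and about 22 in the single setting of Simulation B, with tests near nominal size.

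These figures rest on the assumed 90 countries, effects and country SDs. They show direction and range and do not predict this audit's results. Availability, capacity, shortfall and coverage are descriptive and unaffected.

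**What to change.** Replace the sentence on the Poisson distribution with one that names the model by outcome type, keeping country as the random intercept:

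- Yes/no items (reimbursement, and any referral or barrier item recorded as present/absent): binomial GLMM with logit link, or Poisson log-link with robust standard errors if prevalence ratios are wanted.
- Capacity: negative binomial GLMM with log link, or a linear mixed model on log capacity.
- Referral strategies and barriers: state the response scale of each item, so that the matching model follows from it.

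The cost is a sentence or two of text and a change of distribution and link in the SPSS mixed-model settings. No further data are needed.
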